### 4.5. Sample Size and Power Calculation

To determine the sample size for this study, we considered the change in patients’ overall symptoms measured via the UPDRS from baseline as the primary outcome for our statistical analysis. Based on our pilot study of the effects of TPS in another neurodegenerative condition, we used the smallest effect size of d = 1.5 [31]. We calculated a minimum sample size of 14 participants for a within-group two-tailed paired *t*-test. Although a sample size of 14 subjects is relatively small, it can still provide valuable preliminary data and insights into the feasibility and potential efficacy of the intervention. This pilot study focuses on exploring trends, feasibility, and potential effect sizes rather than achieving statistical significance. However, a sample size of 14 subjects would provide a power of at least 80% (alpha = 0.05) to detect a mean difference of greater than 30% in overall symptom improvement between the pre- and post-stimulation, which is also what our AD study has shown [31]. This AD pilot study with only 10 patients could demonstrate a significant reduction in neuropsychiatric symptoms with large effect sizes (d = 1.5 and d = 2.3). Note, data from trials using MDS-UPDRS when investigating other NIBS therapies (tDCS and TMS) in PD patients was used to estimate the variances for this power analysis, which showed around 20% standard deviation and an effect size of about d = 1.29, even though the studies analyzed other NIBS rather than TPS [67,68]. Although it could interfere with the study power, we do not account for potential dropouts to calculate our sample size due to the preliminary analysis and small sample size. For this reason, the results from our pilot study will inform the design of future larger-scale studies and contribute to developing hypotheses for further investigation.

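### The stated minimum of 14 patients does not follow from d = 1.5 in a two-tailed paired t-test, which gives 6; the error is conservative, but the derivation should be restated

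*Protocol article*

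**What the plan says.** Section 4.5 (Sample Size and Power Calculation) takes change in UPDRS from baseline as the outcome for the calculation. For the planning effect it states "we used the smallest effect size of d = 1.5", taken from the group's own pilot in another neurodegenerative condition. It continues: "We calculated a minimum sample size of 14 participants for a within-group two-tailed paired" t-test. Further on it says that "a sample size of 14 subjects would provide a power of at least 80% (alpha = 0.05"), and gives the target as "to detect a mean difference of greater than 30% in overall symptom improvement between the pre- and post-stimulation".

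The section says that the variances came from trials of other non-invasive brain stimulation in Parkinson's disease, which "showed around 20% standard deviation and an effect size of about d = 1.29". On losses it says "we do not account for potential dropouts to calculate our sample size".

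Section 4.4 confirms that the pre-post comparison is a paired Student's t-test. Section 1.1 cites d = 1.38 on UPDRS part III from an observational study of TPS in Parkinson's disease.

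**The concern.** The article gives the effect size, test, sidedness, alpha and a power level, and rules out a dropout allowance. The sample size can therefore be checked directly, and it does not come out at 14.

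A calculated minimum means that fewer patients would not meet the target. Under the stated inputs, fewer than half of 14 would.

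What is at stake is the description of the design, not its adequacy. A reader is led to think that 14 patients are just enough for a very large effect, when they would detect a considerably smaller one with the same power. Section 4.5 also says that the pilot will inform larger studies, and a derivation that cannot be reproduced is a poor basis for them.

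**Working it through.** **Inputs, all from section 4.5 unless noted**
- Planning effect d = 1.5; alpha 0.05, two-tailed; power at least 80%; dropout allowance none.
- Other effects cited: d = 1.29 (section 4.5) and d = 1.38 (section 1.1).
- Test: paired t-test (sections 4.4 and 4.5).

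**Formula.** For n pairs, the paired t statistic has n − 1 degrees of freedom and non-centrality d√n, where d is the mean change divided by the SD of the change. Power is the probability that a non-central t variable falls outside ± the 97.5% point of the central t distribution. The required n is the smallest that reaches the target power.

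**Attempt to reproduce 14 at d = 1.5**
- n = 5: non-centrality 1.5 × √5 = 3.35, power 0.711.
- n = 6: non-centrality 1.5 × √6 = 3.67, power 0.833. This is the minimum for 80%.
- n = 14: non-centrality 1.5 × √14 = 5.61, power 0.999.

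The stated figure is not reproduced.

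**Required n for a two-sided 5% paired test**

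| d | 80% | 90% | 95% | 99% | Power at n = 14 |
|---|---|---|---|---|---|
| 1.5 | 6 | 7 | 8 | 11 | 0.999 |
| 1.38 | 7 | 8 | 9 | 12 | 0.997 |
| 1.29 | 7 | 9 | 10 | 14 | 0.994 |

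**Could another reading of the inputs give 14?**
- A higher power target at d = 1.5: 14 is reached only at 99.9%.
- d standardised by the SD of the raw score, so that the paired effect is d/√(2(1 − r)) with r the pre-post correlation: r = 0.5 gives 1.5 and n = 6; r = 0 gives 1.5/√2 = 1.06 and n = 10 at 80% power. Reaching 14 needs r = 0 together with 95% power.
- Dropout: inflating 6 to 14 needs a loss of about 55% (6/0.45 = 13.3, rounded up to 14). The article allows for none.

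None of these routes uses the inputs as stated.

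**What 14 patients do provide**
- Smallest d with 80% power: 0.81.
- 95% confidence interval half-width for the mean change: t(0.975, 13)/√14 = 2.160/3.742 = 0.58 SD of the change.
- On the percentage scale, if 20% is the SD of the change: 0.81 × 20% = 16.2%. If 20% is instead the SD of the raw score and r = 0, the SD of the change is 20% × √2 = 28.3%, and the detectable change is 0.81 × 28.3% = 22.9%. The article does not say which SD it means.

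**The case against.** The best defence is that nothing false is claimed about power. At least 80% is a floor, and 14 patients clear it easily. The sentence with the minimum names no power level, and the section says that the pilot is about trends, feasibility and effect sizes more than significance. All of this stands, and it limits the severity. It does not rescue the derivation: the section says that 14 was calculated as a minimum, and at d = 1.5 a paired test gives 14 only at 99.9% power, which the article never mentions.

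Some stronger readings are tempting, but the document does not support them.

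- *That d = 1.5 is wrongly called the smallest effect.* A reader might infer this from the 1.29 and 1.38 cited elsewhere. But the sentence refers to the group's own pilot, whose effects are given as 1.5 and 2.3, and 1.5 is the smaller of those. Using 1.29 or 1.38 gives 7, so neither explains 14.
- *That the inputs contradict each other.* A 30% difference over a 20% SD is 30/20 = 1.5, which agrees with the planning effect. The 1.29 is a result of the trials used for the variance and need not equal the planning value.
- *That a two-group formula was used by mistake.* The normal approximation for two independent groups gives 2 × (1.96 + 0.8416)²/1.5² = 6.98, so 7 per group and 14 in total. The match is suggestive, but other unstated inputs also give 14, such as d = 1.29 at 99% power. The article does not show which was used.
- *That the trial is underpowered, or that dropout threatens it.* At d = 1.5 or 1.29 the opposite is true. The article gives no dropout rate, so any number of completers would be an assumption.

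The naming of UPDRS versus MDS-UPDRS is a separate question and has no bearing on why the result is 6 and not 14.

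**Conclusion.** The point holds in a narrow form. With the inputs that section 4.5 states, the minimum is 6 patients, not 14, and no reading of those inputs as written gives 14. The discrepancy is 8 patients, in the conservative direction. The design has 80% power at d = 0.81, a little over half the planning effect (0.81/1.5 = 0.54).

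This rests on d being standardised by the SD of the change, as a paired t-test requires. If it were standardised by the raw-score SD, the minimum at 80% power would still be at most 10 for any non-negative pre-post correlation. Statements on the percentage scale depend on what the 20% SD refers to, and the article leaves that open.

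This should be fixed. It is not critical, because the power claim is true at 14 and neither the sample size nor the analysis has to change.

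**What to change.** Rewrite the derivation in section 4.5 and leave N at 14:

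- Remove the word minimum and the statement that 14 was calculated from d = 1.5.
- State that 14 was chosen for feasibility. Then give the properties of the design: a two-sided 5% paired t-test with 14 patients has 80% power for a standardised change of 0.81, and the 95% confidence interval for the mean change has a half-width of 0.58 SD of the change score.
- Say whether the 20% SD is that of the change or of the raw score. Give the percentage equivalent (about 16%) only if it is the SD of the change.
- If figures for fewer completers are added, label them as an illustrative assumption.

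If the sponsor did derive 14 from a calculation, the alternative is to state the effect size and power that produce it.

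The cost is a few sentences, with no extra patients, visits or analyses.

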## 5. Expected Results

The proposed study aims to evaluate the safety and efficacy of TPS in addressing both motor and non-motor symptoms of PD, utilizing a sophisticated neuronavigational system to personalize the intervention based on individual patient symptoms and requirements. Despite the inherent limitations associated with this pilot open-label trial—such as a small sample size, absence of a control group, and potential placebo effects—this research can generate critical preliminary data to inform future randomized, double-blinded, controlled studies. We expect to observe significant improvements in motor and non-motor symptoms after 12 sessions of TPS, with remaining effects after a 1-month follow-up. Additionally, the reason for assessing subjects after every three intervention sessions is that we might observe improvements in symptoms such as tremor and loss of smell and taste in less than 12 TPS sessions. Moreover, as TPS, a non-invasive neuromodulation method, is known for its minor side effects, typically limited to mild local discomfort or pressure, we do not expect to observe severe adverse events, proving that TPS is a safe technique for this population.

This study protocol distinguishes itself from other neuromodulation studies through TPS’s capability for individualized, precise, focused brain stimulation that is trackable in real time throughout the intervention. Furthermore, TPS allows pulses to be strategically directed to different brain regions and specific target areas of interest. An additional strength of this protocol is its structured assessment schedule after every three intervention sessions, allowing investigators to evaluate the minimal number of sessions required to achieve significant improvements in patients with PD. It is important to highlight that the TPS equipment can deliver sham stimulation, which maintains the same features as active stimulation but is indistinguishable from active stimulation and replicates all operational aspects such as machine sounds and procedural setup, thereby facilitating blinded controlled trials in the future. In the long term, if TPS proves its safety and efficacy in the PD population, this non-invasive neuromodulation technique can be applied in clinical practice as a targeted-individualized treatment to improve the quality of life for patients living with PD.

## Figures and Tables

**Figure 1 bioengineering-12-00773-f001:**
[figure not shown]
Study scheme of enrollment, intervention, and assessment timepoints along the study period. Follow-up will be performed 1 month after the last stimulation session.

**Figure 2 bioengineering-12-00773-f002:**
[figure not shown]
Study setup for the treatment of a patient with TPS using 3D navigation for personalized therapies.

**Figure 3 bioengineering-12-00773-f003:**
[figure not shown]
Examples of the TPS intervention strategy based on baseline assessments: (**a**) UPDRS-III score > 33 and a BDI score ≥ 14, pulse distribution: 1000 on M1 (each hemisphere), 1000 DLPFC (each hemisphere), and 4000 distributed across the brain areas (as standard intervention); (**b**) UPDRS-III score > 33 and VHI-10 ≥ 11, pulse distribution: 1000 on M1 (each hemisphere) and 1000 inferior frontal cortex extending on the left to Broca’s area (each hemisphere); (**c**) SCOPA-COG ≤ 24 and VHI-10 ≥ 11, pulse distribution: 500 on M1 (each hemisphere), 750 DLPFC (each hemisphere), and 750 inferior frontal cortex extending on the left to Broca’s area (each hemisphere); (**d**) PFS-16 binary score of >8, PDSS-2 score ≥ 18, 500 on M1 (each hemisphere), 750 DLPFC (each hemisphere), and 750 PPC. Additionally, 4000 will be distributed across the brain areas as a standard intervention. Horizontal and vertical lines reflect the position of the Coronal, Sagittal and Axial planes. Circular and oval shapes mark the areas of interest for the intervention.

**Table 1 bioengineering-12-00773-t001:** Representation of the patients’ symptoms and target brain regions of interest for TPS individualized intervention.

Symptoms	Clinical Feature	Test Definition	Brain Region of Interest
Motor impairment	Moderate to severe rigidity, freezing of gait, postural instability, tremor, and bradykinesia	UPDRS-III score > 33	Bilateral and entire strip of the primary motor cortex (M1)
Cognitive impairment	Mild memory and executive function alterations	SCOPA-COG ≤ 24	Bilateral dorsolateral prefrontal cortex (DLPFC)
Psychiatric disorder	Depression	BDI-II score ≥ 14	Bilateral dorsolateral prefrontal cortex (DLPFC)
Sleep disorder	Moderate to severe sleep disturbance	PDSS-2 score ≥ 18	Bilateral posterior parietal cortex (PPC)
Fatigue	Moderate to severe fatigue	PFS-16 binary score of >8	Bilateral dorsolateral prefrontal cortex (DLPFC)
Voice/speech dysfunction	Moderate to severe dysarthria and poor voice control	VHI-10 score ≥ 11	Bilateral inferior frontal cortex extending on the left to Broca’s area
Taste and smell disorders	Moderate or severe olfactory and gustatory dysfunction	VAS for taste or smell ≥ 4	Bilateral orbitofrontal

## Data Availability

Not applicable.

## Abbreviations

The following abbreviations are used in this manuscript:

AD	Alzheimer’s Disease
AE	Adverse Effects
AIM	Acceptability of Intervention Measure
BBB	Blood–Brain Barrier
BDI	Beck Depression Inventory
BDNF	Brain-Derived Neurotrophic Factors
CAPE-V	Consensus Auditory-Perceptual Evaluation of Voice
DBS	Deep Brain Stimulation
DLPFC	Dorsolateral Prefrontal Cortex
EEG	Electroencephalogram
ESWT	Extracorporeal Shock Wave Therapy
FIM	Feasibility of Intervention Measures
FOGQ	Freezing of Gait Questionnaire
M1	Motor Cortex
MRI	Magnetic Resonance Imaging
NIBS	Non-Invasive Brain Stimulation
NMSS	Non-Motor Symptoms Scale
PD	Parkinson’s Disease
PDQ-39	Parkinson’s Disease Questionnaire-39
PDSS-2	Parkinson’s Disease Sleep Scale
PFS-16	Parkinson’s Disease Fatigue Scale
PIGD	Postural Instability And Gait Difficulty
PPC	Posterior Parietal Cortex
PQAT-RW	Patient’s Qualitative Assessment of Treatment–Real-World
QOL	Quality Of Life
RBD	Rapid Eye Movement Sleep Behavior Disorder
SCOPA-COG	SCales for Outcomes in PArkinson’s disease-COGnition
SLT	Speech and Language Therapy
tDCS	Transcranial Direct Current Stimulation
TMS	Transcranial Magnetic Stimulation
TPS	Transcranial Pulse Stimulation
TUG	Timed Up and Go
UPDRS	Unified Parkinson’s Disease Rating Scale
VAMS	Visual Analog Mood Scale
VAS	Visual Analog Scale
VEGF	Vascular Growth Factors
VHI-10	Voice Handicap Index
